### Study procedures

2.4

#### Recruitment, screening, and informed consent

2.4.1

Neonates meeting the inclusion criteria will be prospectively identified and recruited by trained neonatologists from the NICUs and pediatric wards of the 22 participating hospitals. Two attending neonatologists at each site will be responsible for patient enrollment using standardized diagnostic criteria.

Written informed consent will be obtained from the parents or legal guardians after a definitive diagnosis is made. The study adheres to the ethical principles of the Declaration of Helsinki and has received institutional ethics approval.

To ensure rigorous standardization across the 22 participating centres, all enrolling neonatologists will undergo a mandatory centralized training workshop focused on standardized case definitions, MRI interpretation using a validated study atlas, and EEG acquisition protocols. In parallel, to maintain longitudinal data quality, annual inter-rater reliability assessments will be conducted using 10 blinded test cases. For diagnostic adjudication, all stroke subtypes will be centrally reviewed by an expert committee comprising three senior neonatologists and two neuroradiologists at Shenzhen Children's Hospital, who remain blinded to the initial site-level diagnosis. Furthermore, neuroimaging will adhere to a harmonized 3T MRI protocol (including DWI, SWI, and MRA/MRV sequences). Where 3T MRI is not immediately available at a participating center, arrangements will be made for patient transfer to a center with 3T capacity, and this will be documented. Specific scoring approaches for infarct volume (modified Pediatric ASPECTS) and PLIC assessment will be used centrally. All video-EEG recordings will be centrally interpreted by a single epileptologist masked to all clinical and imaging data.

#### Data collection, management, and online registry

2.4.2

Data will be collected using a standardized Excel data collection form (provided as Supplementary File 1). A secure, web-based electronic registry is planned for future public access and multicenter expansion. The registry will capture both inpatient and post-discharge follow-up data, manually entered by trained neonatal attending physicians at each center.
Data Entry and Management: Each participant will be assigned a unique ID. Baseline data (demographics, medical history, MRI scans, EEG, and coagulation function) will be recorded within 24 h of diagnosis.**Follow-up Data Collection**: Follow-up assessments will be conducted at 6 months, 18 months, 3 years, and 5 years (corrected age). The selection of these time points was based on published literature and local clinical practice in China: 6 months is a key age for motor assessment and early intervention (routine well-child visit); 3 years allows comprehensive cognitive, language, and behavioral assessment (preschool entry examination); and 5 years permits assessment of learning disabilities, attention problems, advanced cognitive functions, and social adaptation (preschool exit/primary school entry) (14, 15). Follow-ups can be done at any participating center based on patient preference.Retention Strategies: To encourage follow-up, commemorative gifts will be given on Children's Day (June 1) and patients’ birthdays. For families facing financial hardship, follow-up costs will be covered by the Neonatal Department's funding at Shenzhen Children's Hospital.Governance: A Clinical Research Data Monitoring Committee (chaired by [name]) will oversee protocol compliance, training, progress reviews, data analysis, and reporting.

#### Data elements and database modules

2.4.3

The online registry is divided into the following modules:
General and Hospital Information: Demographics, birth facility data, and administrative details.Family and Perinatal History: Family history, maternal/pregnancy data, labor/delivery details, and resuscitation history.Neonatal Clinical Presentation: Initial Status (e.g., blood glucose), seizure data, and comorbidities.Diagnostic Tests and Biological Samples: Coagulation tests, genetic data (optional), neuroimaging, and EEG results.Treatment and Discharge Summary: Details of therapies, discharge diagnosis, and treatment outcomes.Long-Term Follow-up Examinations: Data from 6m, 18m, 3y, and 5y visits, including Bayley-4C scores, EEG, MRI results, growth metrics, and epilepsy medication.Follow-up Conclusions: Final Status, including outcomes like epilepsy, cognitive impairment, motor disorders, and cerebral palsy, confirmed by pediatric neurologists and rehabilitation physicians.The complete data dictionary is available in Online Supplementary File 3.

#### Standardized diagnostic and outcome criteria

2.4.4

Key research variables are defined as follows:
Neonatal Arterial Ischemic Cerebral Infarction: Ischemic necrosis caused by cerebral artery infarction in newborns.Neonatal Hemorrhagic Stroke: Intracranial or intraventricular hemorrhage in term infants (37–42 weeks GA) within 28 days.Neonatal Cerebral Venous Sinus Thrombosis: Thrombotic occlusion of venous sinuses or cerebral veins.Neonatal Seizures: Abnormal EEG activity with stereotypical, episodic manifestations.Perinatal Maternal Diseases: Includes gestational diabetes mellitus and hypertension.Congenital Heart Disease: Structural anomalies of the heart or major vessels.Neonatal Polycythemia: Venous hematocrit ≥65% in the first week.Twin-to-Twin Transfusion Syndrome: Significant hemoglobin and weight differences between twins.Disseminated Intravascular Coagulation: Systemic coagulation activation syndrome.Early-onset Neonatal Sepsis: Sepsis onset within 72 h of life.Neonatal Hypoxic-Ischemic Encephalopathy: Brain damage from perinatal asphyxia.Neonatal Hypoglycemia and Hyperglycemia: Blood glucose < 2.2 mmol/L and > 7 mmol/L, respectively.Bayley Scales of Infant and Toddler Development (Bayley-4C): At all follow-up time points (6 months, 18 months, 3 years, and 5 years), we use the Chinese version of the Bayley Scales of Infant and Toddler Development, Fourth Edition (Bayley-4C) as the sole standardized instrument. Other validated instruments, such as the Hammersmith Infant Neurological Examination (HINE) and Griffiths Mental Development Scales, are not used in the current protocol but may be considered in future extensions.

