#### Inclusion criteria

2.3.1

Participants must meet all the following criteria:
Gestational age ≥28 weeks and ≤28 days postnatal, with identified stroke risk factors. (Extremely preterm infants <28 weeks are excluded by design due to diagnostic challenges and different pathophysiology.Clinical presentation of acute encephalopathy or seizures.Neuroimaging confirmation (MRI) of stroke (arterial ischemic, hemorrhagic, or cerebral venous sinus thrombosis), excluding other common etiologies. Clinically silent infarctions (incidental findings on imaging without clinical symptoms) will be excluded. To ensure complete case ascertainment, all neonates with identified risk factors for stroke (e.g., congenital heart disease, extracorporeal membrane oxygenation, or severe perinatal asphyxia) will undergo systematic screening with cranial MRI, and any asymptomatic infarctions detected will be documented separately but excluded from the primary analysis cohort**.**Parental or legal guardian consent.

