### Statistical analysis plan

2.7

All analyses will be performed using SPSS (Version 27.0) and R (Version 4.4.1).
Descriptive Statistics: Continuous data will be presented as means ± SD (for normally distributed data) or as medians [IQR] (for non-normally distributed data). Categorical data will be analyzed using Chi-square or Fisher's exact tests.Incidence and Survival Analysis: Registry-based incidence and survival rates will be stratified by gestational age, sex, birth weight, and hospital level.Predictive Model Development:
Predictor Selection: LASSO regression will be used to identify potential predictors.Model Building: Multivariable logistic regression will identify independent factors associated with poor neurodevelopmental outcomes.Model Validation: Internal validation using bootstrap resampling (1,000 repetitions) will assess model performance (discrimination, calibration, and clinical utility).A two-sided *p*-value < 0.05 will be considered statistically significant.

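### Hemorrhagic stroke is defined only at 37–42 weeks while inclusion admits it from 28 weeks with no upper limit, and the incidence denominator matches neither range

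*Protocol article*

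**What the plan says.** Inclusion criteria (2.3.1): the gestational-age criterion reads "Gestational age ≥28 weeks and ≤28 days postnatal, with identified stroke risk factors". The only infants removed on gestational age are those below 28 weeks: "Extremely preterm infants <28 weeks are excluded by design due to diagnostic challenges and different pathophysiology". The imaging criterion is "Neuroimaging confirmation (MRI) of stroke (arterial ischemic, hemorrhagic, or cerebral venous sinus thrombosis), excluding other common etiologies", with no gestational limit attached to any subtype. Acute encephalopathy or seizures and parental consent are also required.

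Standardized diagnostic and outcome criteria (2.4.4): hemorrhagic stroke is "Intracranial or intraventricular hemorrhage in term infants (37–42 weeks GA) within 28 days". Arterial stroke is "Ischemic necrosis caused by cerebral artery infarction in newborns" and venous stroke is "Thrombotic occlusion of venous sinuses or cerebral veins". Neither of these two carries a gestational range.

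Introduction (1): neonatal stroke is defined by subtype and by onset within 28 days of birth, without a gestational limit. The incidence denominator is all live births at the 22 hospitals.

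Primary outcomes (2.5.1) lists registry-based incidence as the only primary outcome. The Statistical analysis plan (2.7) states "Registry-based incidence and survival rates will be stratified by gestational age, sex, birth weight, and hospital level". The Discussion (3) promises analyses by subtype for all primary and secondary outcomes.

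**The concern.** The numerator of the primary outcome depends on which of two stated limits is applied, and only one of the three subtypes is affected. The gestational-age strata and the subtype analyses are where the conflict shows most. In a preterm stratum the hemorrhagic count is either zero by definition or includes preterm intraventricular hemorrhage, and a reader of the results could not tell which rule had produced it. The Introduction itself attributes discrepant published rates partly to differences in case ascertainment, and an unsettled case definition would bring that problem into this registry.

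**Working it through.** The article gives no figure on this point to reproduce. Its evaluable sample, 300 × (1 − 0.10 − 0.20) = 210, reproduces but does not bear on the question. The check is therefore mainly a comparison of stated ranges.

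**Step 1. Ranges side by side**

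| Item | Section | Gestational age |
|---|---|---|
| Neonatal stroke in general | Introduction | no limit |
| Eligibility, all subtypes | 2.3.1 | 28 weeks and above, no upper limit |
| Arterial stroke | 2.4.4 | no limit |
| Venous stroke | 2.4.4 | no limit |
| Hemorrhagic stroke | 2.4.4 | 37–42 weeks |
| Incidence denominator | Introduction | all live births, including those below 28 weeks |

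**Step 2. A test case.** Take an infant of 32 weeks with seizures, an identified risk factor, an MRI-confirmed hemorrhage and consent.
- On the wording of 2.3.1 the infant qualifies.
- On the wording of 2.4.4 the infant does not have hemorrhagic stroke, and fits neither of the other two subtypes.
- An infant above 42 weeks meets the same conflict.
- An arterial stroke at 32 weeks meets both sections.

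**Step 3. If the definition governs: the hemorrhagic rate.** Let N be total live births, s the share of births outside 37–42 weeks, and R the hemorrhagic rate within 37–42 weeks.
- Cases counted = R × (1 − s) × N.
- Reported rate = cases / N = R × (1 − s), so the relative shortfall against R is s.
- The article does not give s. Assuming 0.05 gives 0.95R (5% too low); assuming 0.10 gives 0.90R (10% too low).

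**Step 4. If the definition governs: the gestational-age comparison.** Total stroke in the 37–42-week stratum is arterial + venous + hemorrhagic. In the 28–36-week stratum it is arterial + venous only. Suppose arterial and venous rates were identical in both strata, and let h be the hemorrhagic share of strokes at 37–42 weeks. The preterm-to-term ratio would then be 1 − h with no difference in those diseases. The article does not give h. Assuming 0.10 to 0.50, the ratio would be 0.90 to 0.50 from the definition alone.

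**Step 5. If the inclusion criteria govern: the subtype mix.** Now let s be the share of births at 28–36 weeks, r the preterm-to-term ratio of hemorrhagic rates, and h the hemorrhagic share of all strokes. Births above 42 weeks are ignored here.
- Share of hemorrhagic cases that are preterm = s·r / (s·r + 1 − s).
- Low end (s = 0.05, r = 1, h = 0.10): 0.05 / 1.00 = 0.05; times h = 0.005 of all strokes; times 300 = 1.5, about 2 cases.
- High end (s = 0.10, r = 10, h = 0.50): 1.0 / 1.9 = 0.526; times h = 0.263 of all strokes; times 300 = about 79 cases.

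All three inputs are assumptions. A span of about 2 to 79 per 300 strokes is not an estimate; it shows that the article does not fix the size.

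**The case against.** The strongest reply is that the two sections can be read together. All inclusion criteria must be met, so 28 weeks is necessary but not sufficient; if 2.4.4 fixes what the word hemorrhagic means in 2.3.1, a preterm infant with hemorrhage is simply ineligible. That reading is coherent. For this reason the stronger statement that a reader might infer, that such infants are eligible yet cannot be counted, is not established: it is one of two readings. But the article does not state the joint reading, its only gestational exclusion is below 28 weeks, and the denominator is not restricted to match.

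A second reply is that Recruitment, screening, and informed consent (2.4.1) provides central training on case definitions, annual reliability checks and blinded central review of subtype, and that the data dictionary, which is not shown, may hold the rule. This weakens any claim that 22 sites will each go their own way. It does not settle the matter: no stated rule tells trainers or the committee which limit applies, and central review may never see an infant whom a site did not enroll.

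A third reply is that stratum-specific rates would ordinarily use stratum births, so a term hemorrhagic rate could be obtained from the planned strata. That is fair, but it does not cure the hemorrhagic rate over all live births or the comparison of total stroke between strata.

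Finally, a 5–10% shift in one subtype's rate is small beside the roughly threefold gap between the two Chinese rates that the Introduction cites (8,373 / 2,660 = 3.1). This limits the importance of that one effect, but not of the structural zero.

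**Conclusion.** The point holds as an unresolved conflict between eligibility, case definition and denominator for one subtype. It rests on the printed text and needs no assumption. If 2.4.4 governs, three things follow: hemorrhagic incidence below 37 weeks is zero by definition, gestational-age comparisons of total stroke partly reflect the definition, and the hemorrhagic rate over all live births is too low by the share of births outside 37–42 weeks (5–10% only if that share is assumed). If 2.3.1 governs, the subtype mix changes by an amount that the article does not allow one to compute.

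Two further inferences go too far. A reader might conclude that the overall stroke rate is diluted by 28–36-week births that cannot be cases; but those births can still be arterial or venous cases, so this holds only for the hemorrhagic rate. A reader might also conclude that preterm hemorrhage would dominate the cohort; the article gives neither the preterm share of births nor a preterm hemorrhage rate, and eligibility further requires risk factors, symptoms, MRI confirmation and consent.

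**What to change.** Reconcile the Introduction, 2.3.1, 2.4.4 and 2.7 so that eligibility, case definition and denominator share one stated gestational-age range for each subtype, with both the lower and the upper bound written out. Aligning only the lower bound would leave infants above 42 weeks eligible but undefined.

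Compute each subtype's incidence over live births in that same range, and take births below 28 weeks out of the denominator. If the ranges differ between subtypes, lay out the all-subtype rate and the gestational-age strata so that no stratum is zero by definition. For example, give the all-subtype rate over the range common to all three, and elsewhere mark the undefined subtype as not defined instead of as zero. Which range is right is for the investigators to decide.

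The cost is modest: one definition, the denominators and a table layout, with matching edits to site training, the adjudication instructions and, if needed, the data dictionary. Live births by gestational age are already needed for the planned stratification. Because enrollment was planned from January 2025, infants already assessed with hemorrhage outside 37–42 weeks should be checked against the agreed rule.

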## Introduction

1

Neonatal stroke, defined as an acute focal neurological injury secondary to arterial ischemic infarction, hemorrhagic stroke, or cerebral venous sinus thrombosis occurring between birth and 28 days of life, is a leading cause of permanent neurological disability in infants (1, 2). This cerebrovascular event results in lifelong sequelae such as cerebral palsy, epilepsy, and cognitive impairments, with an estimated incidence ranging from 1 in 1,100 to 1 in 4,000 live births for perinatal stroke; the incidence of strictly neonatal stroke is less well defined but is approximately 1 in 3,000 to 1 in 5,000 live births (3–5) Critically, mortality rates range from 4% to 10%, underscoring its Status as a primary pediatric health concern (6, 7). Despite its profound impact, evidence-based strategies for prevention, acute management, and long-term prognostication remain significantly underdeveloped, with no standardized, population-based surveillance and outcome-tracking systems in many regions.

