#### Secondary objectives

2.1.2

To characterize the clinical presentation, short-term treatment efficacy, and safety of the three subtypes of neonatal stroke: arterial ischemic stroke, cerebral sinovenous thrombosis, and hemorrhagic stroke.To identify significant prenatal, perinatal, and postnatal risk factors for neonatal stroke, and to develop and validate predictive models for risk stratification using a panel of early biochemical and imaging biomarkers.To analyze regional and institutional variations in the diagnostic, therapeutic, and rehabilitative management of neonatal stroke, and to propose evidence-based strategies for optimizing care and standardizing treatment protocols.

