#### Secondary outcomes

2.5.2

Survival status at hospital discharge and throughout the 5-year follow-up period.Neurodevelopmental outcomes at 5 years were defined as a composite based on Bayley-4C scores and clinical diagnoses of impairments (e.g., cerebral palsy, epilepsy).Risk factor characterization (prenatal, perinatal, and postnatal).Performance of the developed prognostic prediction model for adverse neurodevelopmental outcomes.

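### Several postnatal variables in 2.4.4 need not precede stroke onset: later findings can count as risk factors, and sepsis starting after 72 h but before a later stroke has no defined variable

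*Protocol article*

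**What the plan says.** The Introduction of the protocol article defines the disease by its time of occurrence, ending with "cerebral venous sinus thrombosis occurring between birth and 28 days of life". The inclusion criteria (2.3.1) use the same upper limit: "Gestational age ≥28 weeks and ≤28 days postnatal, with identified stroke risk factors". A secondary objective (2.1.2) is "To identify significant prenatal, perinatal, and postnatal risk factors for neonatal stroke", and 2.5.2 lists the characterization of prenatal, perinatal and postnatal risk factors among the secondary outcomes.

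Section 2.4.4 defines the key variables. Four entries are postnatal conditions whose timing relative to the stroke is open:

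- "Neonatal Polycythemia: Venous hematocrit ≥65% in the first week"
- "Early-onset Neonatal Sepsis: Sepsis onset within 72 h of life"
- "Disseminated Intravascular Coagulation: Systemic coagulation activation syndrome"
- Hypoglycemia and hyperglycemia, given as glucose thresholds (below 2.2 and above 7 mmol/L) with no time limit.

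None of the four refers to stroke onset, and the early-onset entry is the only sepsis variable in the list. The nearest timing rule is in 2.4.2, where baseline data, including coagulation function, are recorded within 24 h of diagnosis. Section 2.4.3 adds modules for initial status (with blood glucose as an example), comorbidities and discharge diagnosis. It also refers to a data dictionary in a supplement that is not shown.

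**The concern.** A risk factor for an event has to be present before the event. If a variable is defined by the infant's age, or has no time limit, it can be positive because of something that happened after the stroke. Disseminated intravascular coagulation and abnormal glucose are the plainest cases, since either can first appear in the course of the stroke, its seizures or its treatment. Reporting them as postnatal risk factors would turn complications into apparent causes.

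The 72-h limit on sepsis works in the opposite direction. It leaves out exposure that does precede the stroke whenever both the sepsis and the stroke come later in the neonatal period.

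At stake are the secondary objective and secondary outcome on risk factors. Both errors bear on their postnatal part: conditions that follow the stroke can be overstated, and infection before later strokes can be understated. Because the article plans to use the same form at 22 hospitals, each site would have to settle the order of events in its own way.

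**Working it through.** The plan states no figure on this point, so there is none to reproduce. The check sets each definition against the period in which a case can arise.

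**Inputs.** Case window: birth to day 28 (Introduction; 2.3.1). Polycythemia window: 7 days of life (2.4.4). Sepsis window: 72 h, or 3 days of life (2.4.4). Coagulation and glucose variables: no window (2.4.4). Day of stroke onset, *d*: an illustrative assumption, because the article gives no onset distribution. Day *d* means *d* days after birth.

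**Step 1: is any definition anchored to the stroke?**

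| Variable | Limit in 2.4.4 | Must begin before the stroke? |
|---|---|---|
| Polycythemia | first 7 days of life | no |
| Sepsis | onset in first 72 h of life | no |
| Disseminated intravascular coagulation | none | no |
| Hypo-/hyperglycemia | none | no |

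Other entries are not affected in this way. Congenital heart disease, twin-to-twin transfusion and maternal disease precede the stroke by their nature.

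**Step 2: share of the case window covered.** Sepsis: 3/28 = 10.7%. Polycythemia: 7/28 = 25%.

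**Step 3: part of each age window that lies after the stroke.**

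- Polycythemia, (7 − *d*)/7: *d* = 1 gives 6/7 = 86%; *d* = 2 gives 5/7 = 71%; *d* = 3 gives 4/7 = 57%; *d* = 5 gives 2/7 = 29%.
- Sepsis, (3 − *d*)/3: *d* = 1 gives 2/3 = 67%; *d* = 2 gives 1/3 = 33%; *d* of 3 or more gives 0.
- Coagulation and glucose: there is no window, so a finding at any time after onset qualifies.

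**Step 4: pre-stroke time outside the sepsis definition,** (*d* − 3)/*d*: *d* = 7 gives 4/7 = 57%; *d* = 14 gives 11/14 = 79%; *d* = 21 gives 18/21 = 86%.

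**Step 5: two constructed infants.** One has a stroke on day 2 and a first glucose above 7 mmol/L on day 4. The infant meets the hyperglycemia definition, although the finding came two days after the event. The other has sepsis starting on day 12 and a venous thrombosis on day 15. Day 12 is past the 3-day limit, so the infant meets no sepsis definition, although the infection came first.

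**Step 6: does the baseline rule repair this?** Recording within 24 h of diagnosis limits when baseline items are entered. The clock starts at diagnosis, which comes after onset, so a coagulation result within that limit may still be a post-stroke result.

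**The case against.** The strongest reply is that this is a condensed article. Its collection form and data dictionary are supplements that are not shown, and an ordering rule or onset dates could sit there. That stands as far as it goes: the text supports saying that later findings *can* be counted, not that they *will* be. It does not remove the point. Section 2.4.4 prints its definitions, and a dictionary entry that matches the printed 72-h limit cannot include sepsis starting on day 12.

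A second reply is that 2.4.4 lists diagnostic definitions and never calls them exposure windows. That is fair. However, the article offers no other definition for the postnatal risk factors of 2.1.2 and 2.5.2, so these conditions are the evident candidates. The initial-status module does tie at least one glucose value to presentation, but the hyperglycemia definition is not confined to that value.

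Several stronger readings are tempting, and the document does not support them:

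- *All sepsis before a later stroke is missed.* Sepsis starting within 72 h is captured, and later sepsis may be entered as a comorbidity, although without a standard definition.
- *Polycythemia is a consequence of stroke.* Nothing in the article suggests this. The entry only illustrates an age-based window.
- *The encephalopathy variable has the same fault.* Its definition, "Neonatal Hypoxic-Ischemic Encephalopathy: Brain damage from perinatal asphyxia", ties the cause to birth, so an infarct without asphyxia does not meet it.
- *The prediction model is contaminated.* The article does not name its 6–8 candidate predictors. The model predicts outcome after stroke, so findings after onset can be legitimate predictors.
- *Eligibility or incidence is distorted.* Inclusion requires identified risk factors, but the article does not say that the 2.4.4 list serves that purpose.

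**Conclusion.** The point holds for four postnatal variables: early-onset sepsis, polycythemia, disseminated intravascular coagulation and abnormal glucose. As defined, none has to precede stroke onset. Post-stroke findings can therefore enter the risk-factor results, most plainly for coagulation and glucose. Sepsis starting after 72 h and before a later stroke has no defined variable.

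The size of the resulting error cannot be derived from the article. The shares above (10.7% of the case window for sepsis; 57% to 86% of pre-stroke days uncovered for strokes on days 7 to 21) compare calendar windows. A reader might take them as misclassification rates. They are not, because strokes and these conditions need not be spread evenly over the 28 days.

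The conclusion assumes that the 2.4.4 definitions are used for the risk-factor outcome and that the supplements contain no ordering rule. The consequence is confined to a secondary objective and outcome. The primary incidence estimate is not directly touched. The change should still be made, because the order of events is easy to record at the time and may be impossible to recover later.

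**What to change.** In 2.4.4 and the collection form:

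1. Record the date and time of onset of each of these postnatal conditions, and of the first sign of stroke.
2. For the risk-factor objective and outcome, count a condition only if it began before that first sign. List later ones as complications, and keep a separate category for conditions whose order is uncertain.
3. Define sepsis as onset at any age before the stroke, reported in two groups: up to 72 h of life, and after 72 h.
4. Do not carry the before-onset rule into the prognostic model. State a time of prediction and require every predictor to be known by then. The before-onset rule would wrongly exclude post-stroke findings, including the imaging markers that 2.1.2 intends to use.

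If the data dictionary already holds such rules, it is enough to state them in 2.4.4, together with the wider sepsis variable.

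The cost is a few date-time fields taken from the chart and a revised definition list. Some conditions will have an onset that cannot be placed before or after the stroke, so the uncertain group will not be empty and should be reported.

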#### Long-term follow-up assessment schedule

2.4.6

Follow-up assessments will occur at corrected ages of 6 months, 18 months, 3 years, and 5 years. A schedule detailing the assessments and measures taken at each time point is summarized in Table 1.

**Table 1 T1:** Schedule of long-term follow-up assessments.

Assessment	6 Months	18 Months	3 Years	5 Years
Bayley Scales of Infant and Toddler Development, Fourth Edition, Chinese Version (Bayley-4C)	✓	✓	✓	✓
Growth metrics (weight, length/height, head circumference)	✓	✓	✓	✓
Neurological examination	✓	✓	✓	✓
Seizure/epilepsy assessment	✓	✓	✓	✓
Epilepsy medication review			✓	✓
Video-EEG			✓	✓
Cranial MRI (3T)			As needed	As needed
Cognitive, language, and behavioral assessment			✓	✓
Learning disability assessment				✓
Attention problems assessment				✓
Social adaptation assessment				✓
Final outcome confirmation (cerebral palsy, cognitive impairment, epilepsy)				✓

✓, assessment performed; MRI performed only when clinically indicated. All ages are corrected ages. Bayley-4C, Bayley Scales of Infant and Toddler Development, Fourth Edition, Chinese Version; EEG, electroencephalography; MRI, magnetic resonance imaging.

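### The protocol allows only an infant-and-toddler scale as a standardised instrument at the 5-year visit, which it defines by school-entry domains, so the score part of the 5-year composite is not shown to be valid at that age

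*Protocol article*

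**What the plan says.** Section 2.4.4 of the protocol article sets the measurement rule for all four follow-up visits, the one at 5 years included: "we use the Chinese version of the Bayley Scales of Infant and Toddler Development, Fourth Edition (Bayley-4C) as the sole standardized instrument". It then names two other developmental tools as examples of validated instruments that "are not used in the current protocol but may be considered in future extensions".

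Section 2.4.2 gives the reason for each visit. For the last one it says that "5 years permits assessment of learning disabilities, attention problems, advanced cognitive functions, and social adaptation", and it places that visit at the end of preschool and the start of primary school.

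Table 1 (Section 2.4.6) ticks Bayley-4C at all four visits. In separate rows it ticks a cognitive, language and behavioural assessment at 3 and 5 years. Three further rows are ticked at 5 years only: "Learning disability assessment", attention problems and social adaptation. None of these rows names an instrument.

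Section 2.5.2 defines the endpoint: "Neurodevelopmental outcomes at 5 years were defined as a composite based on Bayley-4C scores and clinical diagnoses of impairments", with cerebral palsy and epilepsy as examples of the diagnoses. Section 2.1.1 includes 5-year neurodevelopment in the primary objective. Section 2.6 sizes the study on the 5-year outcome rate, and Sections 2.5.2 and 2.7 make adverse neurodevelopmental outcome the target of the prediction model.

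**The concern.** The visit is justified by what can be learned about a child at school entry, yet the only standardised tool permitted there is, by its own title, for infants and toddlers. Two things follow.

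First, the domains that motivate the visit have no standardised measure of their own. Whatever is recorded for learning, attention and social adaptation has to be clinical judgement.

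Second, the 5-year composite contains one test score, and that score comes from a scale whose fitness at this age the document does not establish. Deficits in cognition, language or attention that come without cerebral palsy or epilepsy are the ones a test score is there to detect. The Discussion presents long-term neurodevelopment as a main contribution of the study and lists deficits of this kind among those it expects. If the score cannot be interpreted at 5 years, such children are classified by specialist opinion alone. The central blinded review in Section 2.4.1 covers stroke subtype, imaging and EEG, not developmental outcome.

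**Working it through.** **1. The rule against the purpose of the visit.**
- Section 2.4.4: one standardised instrument at 5 years, Bayley-4C, and no other validated instrument.
- Section 2.4.2: the 5-year visit exists for learning, attention, advanced cognition and social adaptation.
- Table 1: separate rows beside Bayley-4C for these domains, three of them ticked at 5 years only.

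There are two ways to read the extra rows. If they use standardised tools, the sole-instrument statement is wrong. If they use none, the domains that define the visit have no standardised measure beyond whatever Bayley-4C covers. Either way the sections need reconciling.

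**2. Support for the scale at age 5.** The article gives no norm range for Bayley-4C, no rule for scoring a child beyond the normed ages, and no reason for using it at 5 years. The evidence in the document is the scale's title on one side and a school-entry visit on the other. That supports *not shown to be valid at 5 years*. It does not establish *invalid at 5 years*.

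**3. What rests on the 5-year composite.** Inputs from Section 2.6: 300 enrolled, 10% mortality, 20% loss to follow-up, 30% outcome rate, 6–8 candidate predictors.
- Evaluable: 300 × (1 − 0.10 − 0.20) = 210, which reproduces the stated figure. With sequential losses, 300 × 0.90 × 0.80 = 216, close to it.
- Events: 0.30 × 210 = 63, inside the stated 60–80.
- Events per variable: 63 / 6 = 10.5 and 63 / 8 = 7.9, against the stated figure of about 10.

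So about 63 events carry the model, and the 30% rate presumes that the composite can be scored at 5 years.

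**4. How many of the 63 depend on the score.** If a share *s* of events could be recognised only through the 5-year Bayley-4C score, and that score were unusable, 63 × (1 − *s*) events would remain. The document gives no value for *s* and no cut-off for the composite, so the loss cannot be computed.

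**5. What remains without the score.** Section 2.4.3 has epilepsy, cognitive impairment, motor disorders and cerebral palsy confirmed by paediatric neurologists and rehabilitation physicians. Table 1 schedules a final outcome confirmation at 5 years that includes cognitive impairment. The diagnostic part of the composite stands.

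**6. Timing.** Recruitment starts in January 2025, so the earliest fifth birthday is January 2030. Corrected age cannot bring it earlier.

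**The case against.** The strongest reply is that the decisive fact is absent. The document states no upper age limit for Bayley-4C, and a word in a title is weak evidence: the same argument would cast doubt on the 3-year visit, which Section 2.4.2 ties to preschool entry. This stands. It is why the point claims only that validity at 5 years is not shown, and why replacing the scale depends on the sponsor's check of the norms. That check should cover 3 years too.

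A second reply is that Table 1 lists assessments, not standardised tests, so clinical assessment in those rows is logically compatible with a sole standardised instrument. It adds that an article may leave the naming of tools to the full protocol or the data dictionary. This is partly right: unnamed tools would not be a finding by themselves. But the article does not leave the choice open. It fixes one instrument for the 5-year visit and says that other validated ones are not used.

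A third reply is that incidence is the only listed primary outcome (Section 2.5.1) and is untouched. That is correct. The 5-year outcome is formally secondary, although Section 2.1.1 puts it in the primary objective and Section 2.6 builds the sample size on it.

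**Conclusion.** The point holds as a conflict between Sections 2.4.2, 2.4.4 and Table 1, with a consequence for the endpoint in Section 2.5.2. The only test score in the 5-year composite comes from a scale not shown to be normed at that age, and the domains that define the visit are denied any other standardised measure. About 63 expected events and the prediction model rest on that composite. The incidence outcome is not affected.

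A reader might infer three stronger claims, and the document supports none of them:
- *Every 5-year score falls outside the norms.* This only restates an assumed age ceiling. The same goes for a predicted ceiling effect in unimpaired children.
- *The composite has no valid content.* Specialist-confirmed cerebral palsy, epilepsy and cognitive impairment remain, so it is compromised rather than empty.
- *A definite number of events is lost.* Assuming that 25–75% of events rest on the score alone gives 63 × 0.25 = 16 to 63 × 0.75 = 47. That share has no source in the document, so the figures are no estimate.

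The conflict between the sections does not depend on the scale's exact age limit. The need to replace the scale at 5 years does.

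**What to change.** - Keep Bayley-4C at 6 months, 18 months and 3 years.
- Have the sponsor state the age range of the Bayley-4C norms. Unless they cover 5 years, replace the scale at that visit with one standardised cognitive test that has Chinese norms for that age.
- Remove the sole-instrument wording in Section 2.4.4 for the 5-year visit, so that standardised measures, such as a parent-report questionnaire, can serve the attention and social adaptation rows already in Table 1. State whether the learning disability row is tested or judged clinically.
- Redefine the 5-year composite in Section 2.5.2 on the age-appropriate score plus the clinical diagnoses, and bring Section 2.4.2 and Table 1 into line.

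The cost is a licence and assessor training for one instrument, plus the loss of same-scale comparison between 3 and 5 years. No data are lost if the change is made before the first 5-year visits in January 2030. After that, a score not collected at the right age cannot be recovered.
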